### **1.5 The PPS measure, stress and Diffuse Noxious Inhibitory Control system (DNIC)**

Changes in DNIC might in part explain the increased pain sensation among chronically stressed people (over reaction of the ascending stimulating nerve signal in combination with a reduced descending and inhibitory nerve signal (Arndt-Nielsen et al. 2010)). This fits with a plausible hypothesis for the effect of daily nerve stimulation (acupressure), where the persons own stimulation followed by control for reducing tenderness seems to result in a restitution of the lost DNIC function, typically for the chronically stressed person.

### **1.6 The effect of the intervention that uses PPS as a biofeedback marker of stress**

The use of PPS as a biofeedback marker in combination with a multifaceted stress handling program has been validated in two bloc-randomized controlled experiments; one smaller with 50 opera singing students (Ballegaard et al., 2011) and a larger with 292 office workers (Ballegaard et al., 2011).

In the first study 50 opera singing students from two different schools were randomized either to an active treatment group or a control group. The active treatment is comparable to the treatment that is used in this study, while the control group had a two hour lecture on general stress handling. Compared to the control group the active group obtained a decrease in pulse (14 %), a decrease in work of the heart measured as PRP (14 %), a decrease in the number of clinical stress signs (67 %), in PPS (35 %) and in the total number of elevated health risk markers (60 %) (all  $p < 0.05$ ) (Ballegaard et al., 2011).

In the subsequent larger study on 292 office workers, the participants were divided

into two groups based on a PPS measurement; very stressed ( $PPS \geq 60$ ) and little to moderate stressed ( $PPS < 60$ ). The very stressed were bloc-randomized and placed in either an active treatment group where they receive a PPS measuring instrument plus a personal guide to the programme in a three month period, or a control group. The results showed that when the active group was compared to the control group, the intervention had had a clinically useful and scientific significant effect in blood pressure (10 %), work of the heart (10 %), serum cholesterol (13 %) and PPS (42 %) (all  $p < 0,001$ ) and with an 80 % response rate (Ballegaard et al., 2011).

In a prospective uncontrolled study on a random selected group of women with breast cancer, the effect of the intervention gave the following results on PPS (Axelsson et al., 2011). The average change was from 78 to 56 in PPS measure, compared to an average change from 74 to 49 among the 60 office workers in the active group of the previously discussed study (Ballegaard et al., 2011). These women also experienced a significant improvement in level of anxiety and depression, and the improvement in PPS was linked to the improvement in level of depression. Furthermore the feasibility was high, more than 90 % of the women were still using the program six months after start (Axelsson et al., 2011).

A prospective, uncontrolled, clinical case-control database study of 10 years with 160 patients with ischemic heart disease (all were candidates for invasive treatment), who used finger palpated tenderness on the sternum as a biofeedback measure of PPS in combination with a comprehensive self-care based stress management program, showed that the intervention had a long lasting beneficial effect on mortality and healthcare expenses (Ballegaard et al., 2004). The three year risk of dying was significant lower than the general Danish population's and there was a considerable decrease in use of medication, number of hospitalization days, and a decreasing demand of invasive cardiologic treatment, which overall led to an approximately 70.000 DKK reduction of the yearly health expenses per patient (based on the costs ten years ago). These patients started with three weeks of acupuncture treatment while the self-care part was the most important contribution for the rest of the observation period (Ballegaard et al., 2004; 1999;1996).

With respect to psychosocial characteristics the patients were found to have similar characteristics as heart patients receiving pharmaceutical treatment at a hospital outpatient clinic, both being significantly different from a group of healthy controlled and a group of patients without heart disease (both  $p < 0.05$ ) (Ballegaard et al., 1996).

In the same study series, it was found that at baseline there was a significant correlation between the degree of depression and the degree of disease measured by NYHA- classification (correlation coefficient  $r = 0.4$ ,  $p < 0.001$ ), and in addition that the degree of depression at baseline correlated independently to the effect measured as change in the NYHA-classification ( $r = 0.6$ ,  $p < 0.001$ ). The intervention was found to have a significant effect on quality of life, need for medication and degree of disease (all  $p < 0.001$ ) measured by NYHA-classification (Ballegaard et al., 1999).

The finding of a beneficial effect in terms of improved survival when stress management is used by patients with ischemic heart disease has recently been confirmed in randomized studies (Gulliksson et al., 2011;Orth-Gomer et al., 2009). Other researchers have shown that sensory stimulation through acupuncture improves capacity and HRV in patients with heart disease (Kristen et al., 2010). Evaluated in a prospective, uncontrolled, clinical case-control database study the same program in patients with stroke has shown to reduce the cumulative 4-year mortality to a level that corresponds to the general Danish population (Magnusson et al., 2010), against an expected excess mortality of 50%. Half of the deaths after stroke can be attributed to ischemic heart disease (Bronnum-Hansen et al., 2001).

Conclusion on an effect of the selected active intervention:

- The PPS measure has shown to be linked to physiological stress, work of the heart, degree of depression and quality of life.
- Two long-term prospective database studies show a pronounced effect on the consumption of healthcare services and survival without risk for the patient. An editorial article in the prestigious JAMA concludes that when the effect is large and the risk small, prospective observation studies are sufficient as a basis for introducing clinical recommendations (Radford and Foody, 2001).

- Psychological questionnaires show that the patients in these observation studies do not differ from heart patient in medical treatment in terms of psychological conditions.
- There has been observed effect in terms of stress reduction in a group of unselected patients (with breast cancer).
- In two prospective randomized studies in people who are engaged in active employment there has been shown effect on the level of stress on the central heart and health risk markers.
- The treatment has in all studies proved harmless. When the intervention has shown its stress reducing value in not-randomized studies with patients with a life threatening disease such as heart disease, stroke and breast cancer, and subsequently shown in randomized studies with a general population in active employment, the next natural step is to examine whether the effect is strong enough to show as stress reducing in a randomized study in one of the groups of patients with a life threatening disease where the intervention has already proven effective – here ischemic heart disease. If the effect is shown to be powerful enough to confirm the earlier findings, now in a randomized study, then the effect is expectedly also strong enough to reduce the stress strain in patients with other life threatening diseases – and in patients with chronic non life threatening illnesses.

## 1.7 The effect of the used heart rehabilitation

The used heart rehabilitation programs show no effect on the cardiac life style risk factors and mainly serve to withhold compliance in relation to the medical treatment (Danish Society of Cardiology, 2010).

## 2. Hypothesis

In the light of the above mentioned, we find it relevant to examine the effect of the active intervention in a prospective randomized design in patients that have been through a heart rehabilitation program, in order to illuminate its eventual value, provided that the intervention was given to Danish heart patients as a supplement

to the existing rehabilitation.

**Hypothesis:** Can a simple, individualized and self-care based intervention program, that frequently uses the PPS measure as a feedback marker of stress followed by nerve stimulation in order to reduce the level of stress, subsequently expecting increased personal empowerment: improved degree of stress, depression, well-being and life quality (QOL) plus a number of factors affecting exacerbation of the heart disease with potential favorable impact on the consumption of healthcare services and long-term prognosis?

It is internationally recognized that there is a link between stress and depression (Grippio and Johnson, 2009). By involving the depression measurement as a way to measure stress reduction, the new stress measurement (PPS) is linked to a known measurement (depression). In continuation of this, it is also recognized that depression has a primary and secondary negative prognostic significance in heart disease and that reduction of depression symptoms has a beneficial influence on the patients' prognosis in regard to "hard" endpoints, meaning hospitalizations, need of operations, relapse and death. The same applies to well-being measured by WHO-5. It will also be interesting if the patients that embrace the new technology have a clinical effect, even though such an effect cannot be proven for the active group as a whole. Therefore the secondary effect variable is the correlation between change in PPS and change in MDI and WHO-5 scores, in the sense that from a cardiac point of view it will be fully satisfactory, if the study shows that heart patients, who get a better PPS also achieves an improved quality of life if their quality of life is impaired at baseline.

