### **6.2 Secondary effect variables:**

1. Physiological measurements of stress: Level of stress measured by PPS by the same blinded nurse (trained in PPS measurement) at baseline and after three months of observation.
2. The WHO-5 questionnaire measuring well-being (QOL) (Folker and Folker, 2008).
3. Correlation between changes in PPS and changes in MDI and WHO-5 scores respectively.

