## 11. Statistics

### 11.1 Power and calculation of the size of the study population

The primary analysis is based on the depression score of the MDI questionnaire. The prevalence of depression measured as a MDI score  $\geq 20$  was found to be approximately 20 % in patients with ischemic heart disease (Olsen et al 2003; Bech P 2001). In a study with 292 office workers, the prevalence of a MDI score  $\geq 20$  was twice as high in people with a PPS measure  $\geq 60$  compared to people with PPS  $< 40$  (Ballegaard et al 2011). Against this background, it is estimated that among patients with ischemic heart disease who at the same time have an elevated PPS measure the prevalence of an MDI  $\geq 20$  is increased by 80 % compared to patients with ischemic heart disease as a whole, i.e. 36 %.

The Minimal Important Difference (MID) is set at 0.4 when the effect of active treatment is compared to control treatment. MID in terms of improvement of a MDI score is set at 5 points on the MDI scale when the active and control groups are compared. The standard deviation of improvement in both groups is set at 9 units on the MDI scale. Alfa is set at 5 %, Beta at 20 %. Against this background, 50 patients with an MDI score  $\geq 20$  are required in each group, thus 300 patients in total when safety margins of 10 % of the estimated values are included.

An interim analysis on the first 60 patients included showed, that the anticipated prevalences for MDI score were different than found. Therefore the cutpoint on the MDI scale was changed to MDI score = 15.

- Effect size is calculated from all included patients (on intention to treat basis)
- Effect size is a fraction that consists of the difference in a MDI score from before intervention till after treatment for the active group, minus the same

difference for the control group divided by the spread of the change in MDI score, when taking all patients together. In a review of all of the 12 SSRI preparations that the FDA has approved for treatment of depression, the average effect size is 0.3 (Turner et al., 2008). Example: the MDI score in active group changes from 24 to 11 ( $24-11 = 13$ ); while the MDI score for the control group changes from 24 to 14 ( $24-14 = 10$ ). This change in the MDI score is  $13-10 = 3$ ; if the spread (standard deviation) on the MDI score overall are 7.5, the effect size will be  $3/7.5 = 0,4$  ([name], 2010).

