## 11.2 Analysis of the effect variables

Five percent (5 %) will be used as significance level in all statistic tests.

The statistical analysis will look at two groups of cardiac patients separately: 1) those patients for whom all therapeutic approaches have been exhausted and 2) the rest. One joint analysis will be made if it is statistically reasonable. The statistics are compiled on an "intention to treat basis"; meaning that all enrolled patients are included in the subsequent analysis.

In the statistical analysis, subgroup analysis will be made for the patients with the highest PPS values: e.g. all patients with  $PPS \geq 75$ ; or for the highest quartile of PPS values.

"Closed test procedure" will be used to analyze data after 3 and 12 months in terms of the assessment of the treatment effect:

- First priority hypothesis: The Ull Care program improves the degree of depression measured by a MDI depression score, measured after 3 months of intervention.
- Second priority hypothesis: The Ull Care program improves health economic variables, measured after 12 months of intervention.
- Third priority hypothesis: The Ull Care program improves the frequency of clinical events, measured after 12 months of intervention.

Baseline measurements will be co-variant variables in relation to the applied stratification variable: the degree of depression measured by the MDI scale. Data from before and after the intervention will be analyzed separately. Delta values for

the active and control group respectively will be compared to analyze a possible treatment effect. All secondary and tertiary effect variables will be analyzed after the intervention through variance and regression analysis. If the premises for the proposed statistical analysis cannot be met, non-parametric analysis is used. Quality-of-life data will be analyzed to meet the directions of each of the questionnaires. All effect data will be presented a unifying table and primary, secondary and tertiary effect variables will be listed.

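### A correlation between change in PPS and change in MDI or WHO-5 is called fully satisfactory when no effect is proven in the active group, but it has no arm contrast and cannot show that the programme works

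*Protocol*

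**What the plan says.** Protocol section 2 remarks that it would be of interest if patients who take to the technology had a clinical effect, "even though such an effect cannot be proven for the active group as a whole". From this it derives, as a consequence, the secondary variable: the correlation of change in PPS with change in MDI and WHO-5. It adds that "from a cardiac point of view it will be fully satisfactory, if the study shows that heart patients, who get a better PPS" also gain in quality of life where this was impaired at baseline.

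Section 6.2 lists the item as the third secondary effect variable: "Correlation between changes in PPS and changes in MDI and WHO-5 scores respectively". It names no comparison between arms. Section 11.2 sets the level for every test: "Five percent (5 %) will be used as significance level in all statistic tests".

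Section 12 defines a positive study by a between-arm difference in MDI, a between-arm difference in PPS and a condition on risk. The correlation is not among these.

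**The concern.** A correlation of two changes, each from baseline to three months, asks whether patients whose PPS fell also felt better. It does not ask whether patients assigned to the programme did better than patients who were not. Randomisation does not protect it, and the control group could show it equally.

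Two mechanisms need no treatment effect:

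- **Shared fluctuation.** If stress and mood vary together over three months, PPS, MDI and WHO-5 move together in both arms.
- **Shared reporting style.** Under section 9.1 the patient applies the pressure on the sternum and decides when to stop. MDI and WHO-5 are self-completed, and section 4 leaves patients unblinded. A patient inclined to report improvement can do so on all three measures.

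The wording matters because section 2 brings the correlation in for the very case where the randomised comparison has shown nothing. A null result on MDI could then be reported with a secondary effect variable that looks favourable but does not measure an effect.

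**Working it through.** **1. The sample size that the correlation would use.** Section 11.1 supplies the inputs: "MID in terms of improvement of a MDI score is set at 5 points on the MDI scale"; "The standard deviation of improvement in both groups is set at 9 units on the MDI scale"; "Alfa is set at 5 %, Beta at 20" per cent. Two-sided testing is assumed.

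- n per group = 2 × [9 × (1.960 + 0.842) / 5]² = 50.9, so 51. The protocol has 50 per group ("Against this background, 50 patients with an MDI score" of 20 or more).
- Total: 100 / 0.36 = 278; with the 10% margin, 278 × 1.1 = 306. The protocol has 300.

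The plan's figure is reproduced closely. The correlation could therefore be tested in about 300 patients pooled, or 150 in the active arm.

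**2. Chance of a significant correlation with no treatment effect.** The protocol gives no correlation r between the change scores, so a range is assumed. With Fisher's transformation, z = atanh(r) × √(n − 3), and the two-sided 5% test is significant with probability Φ(z − 1.96) + Φ(−z − 1.96).

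Example: r = 0.20, n = 300. atanh(0.20) = 0.2027; z = 0.2027 × √297 = 3.49; Φ(3.49 − 1.96) = 94%.

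| Assumed r | n = 300 | n = 150 | n = 54 |
|---|---|---|---|
| 0.10 | 41% | 23% | 11% |
| 0.15 | 74% | 45% | 19% |
| 0.20 | 94% | 69% | 30% |
| 0.30 | >99% | 96% | 60% |

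The last column illustrates the restriction to active patients impaired at baseline. It borrows the 36% MDI prevalence from section 11.1 (0.36 × 150 = 54). That share is an assumption, and section 11.1 itself reports that the prevalences found differed from those anticipated.

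**3. Correlation significant while the randomised comparison is not.** In 3,000 simulated trials of an inert programme with 300 patients, the MDI difference between arms was significant in about 5%, as it should be. The correlation was significant and the MDI difference was not in 37%, 72%, 89% and 94% of trials, at r = 0.10, 0.15, 0.20 and 0.30.

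**4. What the protocol offers on r.** Two reported findings come near, and neither supplies the value.

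- The office-worker study (section 1.4.1.2) gives mean PPS 51 against 61 by MDI group, p = 0.012, n = 292. This implies t ≈ 2.53 and r = 2.53 / √(2.53² + 290) ≈ 0.15. It is a cross-sectional correlation, not one between changes.
- The breast cancer study (section 1.6) linked improvement in PPS to improvement in depression, but it had no control group, so it does not show what happens without treatment.

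**The case against.** The strongest reply is that the protocol's own decision rule is sound here. Section 12 rests on between-arm differences, the ordered hypotheses in section 11.2 leave the correlation out, and the 12-month analyses depend on the success criteria. A reader might infer from section 2 that the trial could be declared positive on the correlation. The documents do not support that: a failed MDI comparison remains a failed trial. This part of the objection stands and limits the point to interpretation and reporting.

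Three further inferences are tempting and also go too far.

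- **That an inert programme would very likely produce the correlation.** This depends on an r that the protocol does not give. At r = 0.10 the chance is 41% pooled and 23% in the active arm. Because the clause speaks of patients who take up the technology and were impaired at baseline, the smaller samples are arguably the relevant ones.
- **That the known link between PPS and depression makes their changes correlate.** It does not follow. In a simulation with stable traits correlated at 0.2 and independent measurement error, the changes correlated at about 0.00. Shared fluctuation or shared reporting is needed; both are plausible, but neither is demonstrated.
- **That regression to the mean creates the correlation.** Selecting on high PPS and impaired quality of life in the same simulation left the change correlation at about 0.01. Selection shifts group means. It would matter if the clause were read as an uncontrolled before-after improvement, but section 6.2 specifies a correlation.

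It can also be said that arm-wise estimation and baseline adjustment belong in a statistical analysis plan. That is fair for the mechanics, but not for the status that section 2 gives to the result.

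**Conclusion.** The point holds as a matter of interpretation. Section 2 gives a non-randomised association the standing of a satisfactory result when the randomised comparison proves nothing, and section 6.2 labels it an effect variable. No value of the correlation, large or small, separates a working programme from an inert one. This conclusion needs no assumption about r.

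How often a misleading result would arise does depend on r. With no treatment effect and r between 0.10 and 0.30, the range is 41% to over 99% in 300 patients and 23% to 96% in 150, with lower figures in an impaired subgroup. The formal verdict under section 12 is unaffected. The correction is worth making, but it is one of wording and labelling, not a flaw in the primary test.

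**What to change.** 1. Delete the clause in section 2 that calls the result fully satisfactory.
2. Relabel item 3 of section 6.2 as a marker-association analysis, estimated within each arm and adjusted for baseline PPS and baseline MDI or WHO-5.
3. State that it is not evidence of efficacy and cannot support the programme if the between-arm MDI comparison fails.

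A complier-average estimate for patients who take up the technology is not a good substitute. Home visits and telephone calls in an open trial make it doubtful that assignment acts only through compliance, and the method merely rescales the intention-to-treat difference, so a null result stays null.

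The cost is a change of wording and a simple re-specification on data already collected. The sponsor gives up a fallback claim. The correlation remains usable for its legitimate purpose, as information on PPS as a marker.

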### **3. Purpose**

The study has two main purposes:

- 1) **To test, based on the data from the baseline study, whether:**
  - There is a connection between the PPS measure and chronic stress measured as quality of life, occurrence of depression, heart rhythm variability and work off the heart in patients with ischemic heart disease.

- There is a connection between PPS and chronic stress estimated as a forerunner of metabolic syndrome. Metabolic syndrome is in this study primary valued based on decreased insulin resistance/disturbed sugar metabolism.
- There is a connection between PPS and chronic stress measured as altered body fat distribution, i.e. altered relationship between android and gynoid fat distribution.

